## Abstract

**Background:**

In an effort to ensure that all physicians have access to valid and reliable evidence on drug effectiveness, the Italian Drug Agency sponsored a free-access e-learning system, based on *Clinical Evidence*, called ECCE. Doctors have access to an electronic version and related clinical vignettes. Correct answers to the interactive vignettes provide Continuing Medical Education credits. The aims of this trial are to establish whether the e-learning program (ECCE) increases physicians' basic knowledge about common clinical scenarios, and whether ECCE is superior to the passive diffusion of information through the printed version of *Clinical Evidence*.

**Design:**

All Italian doctors naïve to ECCE will be randomised to three groups. Group one will have access to ECCE for *Clinical Evidence *chapters and vignettes lot A and will provide control data for *Clinical Evidence *chapters and vignettes lot B; group two vice versa; group three will receive the concise printed version of *Clinical Evidence*. There are in fact two designs: a before and after pragmatic trial utilising a two by two incomplete block design (group one versus group two) and a classical design (group one and two versus group three). The primary outcome will be the retention of *Clinical Evidence *contents assessed from the scores for clinical vignettes selected from ECCE at least six months after the intervention. To avoid test-retest effects, we will randomly select vignettes out of lot A and lot B, avoiding repetitions. In order to preserve the comparability of lots, we will select vignettes with similar, optimal psychometric characteristics.

**Trial registration:**

ISRCTN27453314

## Background

### Continuing Medical Education for health professionals

In the last decade many countries have legislated within their health systems the revalidation and recertification of medical practitioners [1]. Two principles underlie Continuing Medical Education (CME): professional development is a process of lifelong learning in practice, and professionals must be able to demonstrate they are clinically competent in certain roles. Many countries are facing the challenge of building a formal, sustainable assessment of skills through education programs, accredited providers, acquisition of credit points, and voluntary or mandatory regulation[1]. Although it has been claimed that CME should also include managerial, psychosocial and communication skills to reflect the multidisciplinary context of patient care[2], usually professional development is mainly based principally on advanced clinical subjects. Traditional knowledge transfer formats employ live interactive classes supported by paper-based text and graphic materials; online learning is increasing popular, supported by screen-based text and graphics with different levels of interactivity.

### CME in Italy

A compulsory system of CME was introduced in Italy for all health professionals in 1998. During the five-year cycle from 2002 to 2006, health professionals have been required to earn a total of 150 credits [3]. A national education committee defines the educational standards, accredits educational events, and sets the number of credits earned. A credit involves one hours' learning, *i.e*., one hour of education is worth one credit, but there is a weighting towards activities that present evidence-based (EB) information and are free of commercial interests. The traditional form of acquiring CME credits is to attend lectures and conferences; it is more rare for doctors to be exposed to small group interactive events. Between 2004 and 2005, the committee approved and evaluated the provision of distant learning programmes: 136,208 health professionals (46,952 doctors, 34%) earned 737,603 credits, a result welcomed as a large success [4].

### Dissemination of independent information in Italy

In an effort to ensure that all physicians have open access to valid and reliable evidence on drug effectiveness and safety, the Italian Drug Agency (AIFA) launched a program to disseminate independent, unbiased information. The agency did this by translating into Italian *Clinical Evidence*, a compendium of the best available evidence on treating a wide range of common conditions (Figure 1), and freely distributing it. By 2006, the fourth Italian edition (based on *Clinical Evidence*, Vol. 14) had been published. The online version is freely available to all practicing 248,000 doctors, and 47,000 general practitioners (GPs) receive also a free copy of the concise version of the book.

**Figure 1 F1:**
[figure not shown]
Clinical Evidence.

Interest in EB health care is growing in Italy, although its impact upon clinical practice is still not clear. In 1999, the first pilot free distribution of 50,000 copies of *Clinical Evidence *was assessed through a survey exploring doctors' judgement of its validity, relevance, and usability. The findings indicated that the compendium had been well-received, and confirmed doctors' preference for problem-driven information and the key role of strong endorsement from health authorities for its implementation [5]. However, another survey funded by the Smith Kline Foundation showed that Italian GPs were satisfied with the information provided by pharmaceutical sales representatives, who they considered complete and sufficiently reliable [6].

In order to make certain it was worth the expense of disseminating *Clinical Evidence *and to speed up the diffusion of EBM, AIFA sponsored a free-access e-learning system, based on *Clinical Evidence*, called ECCE (the Italian acronym for Continuing Education Clinical Evidence). ECCE became accessible to all physicians in March 2005 after a pilot period. The results of the first year of use (until February 2006) are reported in detail elsewhere and summarised in Figure 2[7].

**Figure 2 F2:**
[figure not shown]
**Use and average respondents' opinions of ECCE by registered doctors**[7].

### The potential role of e-learning from transferring information to modifying clinical practice

Several conceptual models have been developed for assessing knowledge and competence. A popular one proposed by Miller identifies four stages of development: 'knows, knows how, shows how, and does' that are the essential facets of clinical competence [8]. An individual progresses through cognitive and behavioural steps, from acquiring knowledge to performing a task in practice. Miller's theory assumes that competence predicts performance. Other proposed models consider other influences on a doctor's performance [9], including system-related factors (government incentives, guidelines) and individual-related ones (patient's expectation, relationship with peers) with increasing levels of complexity.

For the purposes of this trial we will adopt Miller's simpler model. The stages of development have been slightly changed to better reflect the different components and skills targeted by educational interventions focusing on EBM: 1) factual knowledge or basic learning: knowing the benefits and risks of different interventions (*e.g*., in patients with unstable angina, aspirin is beneficial); 2) deep learning or competence: posing structured clinical questions considering patients, treatment, comparison, and outcomes and understanding quantitative aspects (relative or absolute risk reduction, number needed to treat); 3) point-of-care ability or performance: the incorporation of EB information into practice, with the adoption of proven treatments and interventions that can potentially improve patients' health. The modified EBM Miller's model is shown in Figure 3.

**Figure 3 F3:**
[figure not shown]
**Miller's model modified to consider different steps of knowledge, competence and performance of EBM**. In this model, the learning ability of ECCE decreases from knowledge to performance (in yellow).

ECCE is thought to directly affect superficial learning (ability to reproduce facts) and, with decreasing impact, deep learning (ability to apply concepts and skills in the workplace) [10]. ECCE's impact on clinical behaviour and patients' outcomes is less straightforward: we prefer to adopt a conservative framework considering phases that necessarily follow one another [11]. Therefore, in this study we want first and foremost to show an improvement in physicians' knowledge, which may or may not affect competence and, finally, on behaviours and patients' outcomes.

### Aim of the study

This trial will test the effectiveness of ECCE e-learning program for transferring EB information to medical doctors after a median of three months of ECCE usage, and retention of the information after a median period of six months. The main hypotheses to be tested are: 1) Does an e-learning CME program based on *Clinical Evidence *and clinical vignettes (ECCE) increase physicians' basic knowledge about epidemiology, therapy, prognosis, and risk factors in a clinical scenario? 2) Do physicians retain the knowledge from the ECCE for more than six months? 3) Is this educational intervention superior to the passive diffusion of information through the printed version of *Clinical Evidence*?

The secondary hypotheses are: Does ECCE modify physicians' attitudes to EB behaviours in a simulated realistic clinical scenario?

## Methods

### ECCE: An E-learning CME Program

ECCE is an e-learning CME tool that uses interactive clinical vignettes based on chapters in *Clinical Evidence *and a predefined sequence of questions. ECCE has four components: 1) the *Clinical Evidence *chapter (*e.g*., headache, chronic tension-type); 2) a clinical vignette from the *Clinical Evidence *chapter that presents a plausible medical scenario (*e.g*., Margaret says to her family doctor: "This time I didn't come for me, but to talk about Rachel, my 25-year-old daughter....); 3) questions addressing the recall of *Clinical Evidence *facts or their application to the medical scenario, from which the doctor is to select the correct answer; 4) the potential answers (*e.g*., a list of potential efficacy descriptors for a therapeutic regimen relevant to the theme); and 5) instructions on what to do (*e.g*., "more than one answer may be correct").

Figure 4 gives an example of a vignette from ECCE. The response option includes one or more correct answers for each question, and other reasonably plausible but incorrect response as distractors.

**Figure 4 F4:**
[figure not shown]
**Example of an ECCE vignette.** We present the first step of the headache (chronic tension-type) vignette and related questions. The vignette was developed from Headache (chronic tension-type), Clinical Evidence.

Vignettes are intended to replicate real-life circumstances as seen by an ordinary GP in everyday practice. Whilst GPs are the primary target of ECCE, many vignettes are also relevant to specialists. Each vignette has a narrative with events and clinical details presented in chronological order: the history evolves with new information from diagnostic tests or additional information reported by the patient. All vignettes use news media techniques, sometimes with fictional or interactive elements (*e.g*., mystery fiction, the possibility to order tests and obtain results in real time, test appropriateness and cost). Users solve the single steps though a question and answer decision system. They gain credits upon completing all steps where they reach a score of 80% or more of the total. Vignettes provide one or two credits depending on the number of questions. Users are required to finish the vignette started regardless of the score reached. If a user fails, the vignette is then not used again for 24 hours. In 2005, we posted 120 vignettes, and in 2006, 52 new ones.

Both clinical vignettes and related questions will be carefully planned against *Clinical Evidence *chapters by ECCE authors who are all specialised medical practitioners. Standardised guidelines will be developed by the ECCE editors to help authors. Author guidelines will consider system rules (*i.e*., each question has five multiple-choice answers), writing style (avoid misleading constructs such as double negatives), medical style (avoid excessive technical jargon, such as *rigor nucalis*) and provide an example framework. Each vignette will be revised by two editors to ensure it is appropriate for the *Clinical Evidence *chapter tested. All vignettes will be copy-edited to high editorial standards. Although this would be a highly standardised process, a skilled clinical vignette writer is essential for valid assessment of doctors' abilities and competencies [12].

ECCE has all the standard advantages of e-learning. Users select what and when they want to learn, and at what pace. The system is easy to use and works with basic computer requirements (*e.g*., low speed connection). The contents of *Clinical Evidence *can be read on-screen or printed and interactively managed along the steps of each vignette. The system tracks learning content and the learner's progress.

### Study design

This is a before and after pragmatic randomised controlled trial utilising a two-by-two incomplete block design. When evaluating educational interventions aimed at improving clinical practice, a number of non-specific effects may influence estimates of the effect of an intervention, grouped together under the term Hawthorne effect [13-17]. These include positive attention effects, caused by participants knowing that they are the subject of a study, but also negative and demotivating effects, caused by being allocated to a control rather than an intervention group. If these non-specific effects are imbalanced across study groups in a quality improvement trial, the estimates may be biased. Randomised controlled trials using balanced incomplete block designs should balance such non-specific effects [13,15,17-20].

Because the Hawthorne effect may influence the outcome, this trial will adopt a two-by-two balanced incomplete block design in which subjects will be randomised into two groups. Group one will have access to ECCE for *Clinical Evidence *chapters and vignettes lot A and will provide control data for *Clinical Evidence *chapters and vignettes lot B. Group two will have access to ECCE for lot B and will provide control data for lot A. The design will be balanced because it ensures that all participants receive the same intensity of educational intervention and data collection, which should therefore balance any non-specific effects. The design will be incomplete because not all participants receive the complete education for all chapters and vignettes [14,17]. To check for a possible Hawthorne effect we will add a third control arm (classical design), with only a minimal intervention consisting of one of the elements of the complete intervention, namely the concise printed version of *Clinical Evidence *and access to the on-line full-text version. This group will not have access to the ECCE platform nor the clinical vignettes related to *Clinical Evidence*. The incomplete block design will answer the question "Does ECCE increase physicians' basic knowledge about EB information," while the classical design will answer the question "Is ECCE superior to the printed version of *Clinical Evidence." *Table 1 summarises the block and the classical designs.

**Table 1 T1:** Designs, hypotheses per trial, and possibility of ensuring equal Hawthorne effect across the arms.

Trial comparison	Design	Hypothesis	Hawthorne
Arm I vs. II Complete intervention on lot A. Using lot B as control.	Block	If the test scores related to lot A vignettes increase in accordance with *Clinical Evidence *chapters A and there is no change in test scores of B chapters, the intervention has a genuine effect.	No
Arm II vs. I Complete intervention on lot B. Using lot A as control.	Block	If the test scores related to lot B vignettes increase in accordance with *Clinical Evidence *chapters B and there is no change in test scores of A chapters, the intervention has a genuine effect.	No
Arm I vs. III Complete intervention for lot A (ECCE). Minimal intervention on A-B chapters (*Clinical Evidence*) (control).	Classical	If the test scores related to A vignettes in the intervention arm increase in accordance with the *Clinical Evidence *chapters A and there is no change in the control arm the intervention (ECCE) has a favourable effect, but without controlling for the Hawthorne effect.	Yes
Arm II vs. III Complete intervention for lot B (ECCE). Minimal intervention on A-B chapters (*Clinical Evidence*) (control).	Classical	If the test scores related to lot B vignettes in the intervention arm increase in accordance with the *Clinical Evidence *chapters B and there is no change in the control arm the intervention (ECCE) has a favourable effect, but without controlling for the Hawthorne effect.	Yes

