### Study participants

This study will involve Italian doctors naïve to ECCE who voluntarily agree to participate. Doctors can learn about this research program through advertisements in medical journals and websites. New users who enter the ECCE website will be automatically invited to participate. There will be no exclusion criteria.

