### Sample size and calculation of power

Based on a preliminary examination of test scores, we established that the smallest useful difference for this intervention was a 20% absolute improvement. Based on a preliminary test of 300 doctors, we found that a 28% absolute improvement was due to the intervention. We standardised the absolute improvement across different type of vignettes (five or ten questions). Therefore we calculated our sample size to detect a 0.7 standardized difference in the primary outcome, set the α error rate at 0.05 (two-sided), and the β error at 0.10 (90% power). This yielded a sample size of 45 practitioners per study arm. If the accrual period is six months, and the maximum follow-up period is six months with a loss during follow-up of 20% at the end of the study, the total number of practitioners to be randomised has been adjusted upwards to 162 (54 per intervention group).

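### Arm III's exclusion from credit-bearing ECCE vignettes puts the ECCE-versus-print comparison at risk of unequal drop-out and test effort, and no described measure offsets this

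*Protocol article*

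**What the plan says.** The Abstract ties credits to the vignettes: "Correct answers to the interactive vignettes provide Continuing Medical Education credits". The section on the ECCE program puts this at one or two credits per vignette, earned at a score of 80% or more. CME in Italy describes a compulsory system with 150 credits to be earned over 2002 to 2006.

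Under Study design, arm III receives the concise book and the online text, and "This group will not have access to the ECCE platform nor the clinical vignettes". Under Intervention, the platform is closed to arm III during the intervention period. Afterwards a sample of vignettes opens to arms I and II until the trial ends; arm III is not mentioned.

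ECCE is not otherwise restricted: "ECCE became accessible to all physicians in March 2005 after a pilot period". One recruitment route is the site itself: "New users who enter the ECCE website will be automatically invited to participate".

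Study design lists among the threats to such trials "negative and demotivating effects, caused by being allocated to a control rather than an intervention group", and says that imbalance in these effects may bias the estimates. In Table 1, both comparisons with arm III are described as not controlling for the Hawthorne effect. Study design nevertheless says that the classical design will answer whether ECCE is superior to print, which is main hypothesis 3. The sample size section assumes a single "loss during follow-up of 20% at the end of the study".

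**The concern.** A doctor who comes to the ECCE site and is allocated to arm III is shut out of the programme that drew them there. They receive material that, according to the Background, is already online for all practising doctors and is sent in print to 47,000 general practitioners. Arms I and II can earn ECCE credits and keep some vignette access up to post-test two. All three arms are volunteers who are followed by e-mail at about weeks 16 and 36.

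Two things could then depend on allocation: who sits the post-tests, and how hard they try. Either would distort the comparison of arms I and II with arm III without any difference in knowledge gained. The protocol describes this kind of demotivation itself. The block design balances it between arms I and II, but nothing described does so for arm III, which carries main hypothesis 3.

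**Working it through.** **1. The plan's own figure.** Inputs from the sample size section: "Therefore we calculated our sample size to detect a 0.7 standardized difference in the primary outcome", two-sided alpha 0.05, 90% power.

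- Normal approximation: n = 2(1.960 + 1.282)² / 0.7² = 42.9, so 43 per arm.
- The t-test solution is 43.9, so 44. The stated 45 is within 2 of both.
- Loss adjustment: 45 × 1.20 = 54, and 3 × 54 = 162, as stated.
- An equal 20% loss leaves 54 × 0.80 = 43.2 per arm, with t-test power of 89.5% for one ECCE arm versus arm III.

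**2. What unequal loss does to power.** The documents give no loss by arm, so the losses below the first row are assumptions. Two-sample t-test, difference 0.7 SD, 54 randomised per arm:

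| Loss, ECCE arms / arm III | Left in arm III | One ECCE arm v III | I+II v III |
|---|---|---|---|
| 20% / 20% (plan) | 43.2 | 89.5% | 96.1% |
| 15% / 30% | 37.8 | 88.3% | 94.9% |
| 20% / 40% | 32.4 | 84.4% | 92.1% |
| 20% / 50% | 27.0 | 80.3% | 88.2% |

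Even a marked imbalance leaves power at 80% or above, so the single 20% is not a material sample size error.

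**3. What unequal loss does to the estimate.** The planned analysis is a repeated-measures ANOVA with a pre-test, so the relevant quantity is the gain from pre-test to post-test. Let p be the proportion lost in an arm, and D the mean gain of completers minus the mean gain that those lost would have shown. The arm's true mean gain is (1 − p) × completers' gain + p × lost doctors' gain, so completers overstate it by p × D. The error in the ECCE-minus-print contrast is therefore

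p(ECCE) × D(ECCE) − p(III) × D(III).

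A difference in level that is the same at pre-test and post-test cancels. The error arises when those who leave would have gained a different amount and the products differ between arms. If D is the same positive value in all arms and arm III loses more, the error runs against ECCE. The documents give neither p by arm nor D.

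**4. What unequal effort does.** If arm III doctors stay but try less at the post-tests than at the pre-test, their measured gain is too small and the error favours ECCE. This can act together with step 3 and in the opposite direction, so the sign of the net error is unknown.

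**5. Which comparison is exposed.** Arms I and II have matching access to credits, each through its own lot, so the incentive is balanced between them. The exposure is confined to comparisons with arm III.

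**The case against.** Several stronger readings are tempting, and the article does not support them.

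- *Drop-out and effort will differ.* No section predicts this. The text supports a risk only.
- *Arm III can earn no CME credits.* It cannot earn ECCE credits through vignettes. It can attend other CME, which the trial records. The article does not say whether the knowledge tests carry credit, for any arm.
- *Leaving the trial restores ECCE access.* Withdrawal is not described, so this is inference. Nor is it known how many participants come through the site, since journal and website advertisements are also used.
- *Credit-driven study is itself bias.* It is not. ECCE is a credit-bearing programme in a pragmatic trial, and study prompted by credits is part of what is compared with print.
- *The bias can be given in SD units.* Any such figure needs invented losses and score gaps. A comparison of completers' raw post-test means would also ignore the planned pre-test to post-test contrast.

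The best defence is that the matter is partly disclosed and partly handled. Study design names demotivation, Table 1 concedes the uncontrolled effect, and arm III was added to check for a Hawthorne effect. Follow-up covers all arms by e-mail, analysis is by intention to treat, and drop-out and satisfaction are to be examined. Arms I and II are also restricted, to one lot each, whereas 120 + 52 = 172 vignettes had been posted.

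Most of this stands, and it limits the point. But Table 1 mentions neither credits nor attrition. An intention-to-treat principle does not supply scores that were never given, or separate low effort from low knowledge. The later vignette access for arms I and II only is a stated choice that widens the gap up to post-test two.

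**Conclusion.** The point holds as a risk to main hypothesis 3, of unknown size and direction. It rests on stated features: credits attached to vignettes that arm III cannot open, later vignettes for arms I and II only, recruitment partly from new ECCE users, and open access to ECCE outside the trial. It also assumes that access to ECCE credits affects willingness to return and to try. That is plausible in a compulsory credit system, but the documents do not demonstrate it.

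The protocol's statement that the classical design will answer the superiority question is firmer than its own Table 1 allows. The effect on power is secondary, and arm I versus arm II is untouched. This is an inexpensive improvement to make before enrolment, not a flaw that invalidates the trial.

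**What to change.** 1. In Intervention, add that doctors are told at enrolment that arm III receives full ECCE access, with credits, directly after its own post-test two. Cost: one sentence in the invitation and later access for 54 doctors. Some arm III doctors may postpone study in anticipation.
2. If accreditation allows, give the same fixed credit for completing each knowledge test in all three arms, regardless of score. Cost: accrediting up to 162 × 3 = 486 completed tests, and a setting slightly less like ordinary practice, equally in every arm. This gives all arms the same reason to attend; it does not by itself guarantee effort, and it leaves the ECCE vignette credits in place as part of the intervention.
3. Report loss by arm at post-test one and post-test two.
4. In Study design or the Discussion, state that the ECCE-versus-print result remains open to non-specific effects, including unequal retention and effort, so that it agrees with Table 1.

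No additional participants are needed.
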